## Trial design {8}

A cluster-randomized controlled superiority trial will be performed in 30 schools in three cities (15 controls and 15 in the experimental group), with a total of 3800 children participating in the test (1900 in the control group and 1900 in the intervention group). This study is a randomized controlled trial with two parallel groups (intervention and control) of students aged 6 to 10 years and enrolled in the first to fourth year of elementary education in public schools in the cities of Fortaleza, Eusébio and São Paulo, which are located in the states of Ceará and São Paulo. The ratio of intended numbers of participants in each of the comparison groups is 1:1. The control group receives treatment as usual in Brazil, i.e., no behavioural intervention at the school.

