## Interventions

### Explanation for the choice of comparators {6b}

Among the schools selected to participate in the study, a second simple randomized selection will define the control and experimental schools at a ratio of 1:1 control and experimental schools per municipality. The selected comparison group is treatment as usual, which means no behavioural interventions delivered in the control schools. This is a suitable comparator, as it is the standard experience of schoolchildren in Brazil. Public schools for children in Brazil do not usually receive interventions to improve behavioural skills.

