## Assignment of interventions: allocation

### Sequence generation {16a}

The allocation of schools (1:1) to the control or intervention group will be performed via simple random drawing from the list of the Anísio Teixeira National Institute of Educational Studies and Research (INEP, its acronym in Portuguese), which includes all Brazilian schools separated by city. Randomization will be performed using a quantitative methodology in PASS 15 Efron’s biased coin (two treatments, equal sample sizes). The target sample sizes are the same for both groups. To achieve a longitudinal balance between groups, the algorithm dynamically changes the group assignment probabilities.

The unit of randomization between groups is the schools and not the classes. Therefore, there will be no control classes in an experimental school and vice versa to avoid sample contamination. Agreement to participate in the study was received from the schools before randomization.

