### Concealment mechanism {16b}

Only 30 of the eligible schools will join the trial based on our pre-estimated sample size. The initial selection of 30 schools will use www.random.org. All of the schools’ names will receive a number from one to the total number of eligible schools (i.e., if there are 42 eligible school names, then each one will receive a number from 1 to 42). A random number generator will select 30 numbers from a range of 1 to the total number of eligible schools. These 30 numbers will be randomly assigned to control or intervention groups using Efron’s biased coin to ensure balanced groups. All schools recruited in the same city will be randomized simultaneously. Randomization within each city will be performed when all schools are recruited for that city, rather than waiting until all schools (across all cities) are recruited and then performing randomization of all schools simultaneously. Members of the trial team who are involved with recruitment of schools will be unaware of previous allocations. Trial researchers, not involved with school recruitment, will inform schools of their randomized allocation.

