## Data collection and management

### Plans for assessment and collection of outcomes {18a}

The main outcome of the study is the behavioural repertoire of the children, including problem behaviours, such as disruptiveness, aggressiveness and shyness, and prosocial behaviours. We will control for covariates, such as the gender and age of teachers and children, and the teachers’ stress levels and senses of self-efficacy. The main outcome will be collected using the TOCA-C, which is an instrument to measure the social adaptation behaviours of elementary school students. The teacher answers the 21 items of the instrument and classifies the frequency of each student’s behaviours in the classroom on a Likert scale (ranging from “never” to “almost always”). The TOCA-C was designed to investigate disruptive behaviours or problems with concentration and social skills [42]. The instrument was translated by the team of researchers responsible for the project, who will also perform validation and cultural adaptation to Brazil. Covariates will be collected using the Student-Teacher Relationship Scale-Short Form (STRS-SF), which is a sociodemographic questionnaire on age, gender, education and length of professional experience. Teacher socioeconomic status will be collected using the Index of the Brazilian Association of Research Companies. Sense of competence will be assessed using the Bäbler and Schwarzer General Self-Efficacy Scale as adapted by Gil-Monte and Moreno-Jiménez. Teachers’ mental health will be assessed using the Self-reporting Questionnaire (SRQ 20).

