## Statistical methods

### Statistical methods for main outcomes {20a}

Four two-level regression analyses for the observed continuous dependent measures will be performed (one analysis for each subscale of the TOCA and one for TOCA general score; disruptiveness, concentration problem and prosocial behaviour). Each grade has a teacher who is responsible for the implementation of the Elos 2.0, and consequently, teacher and classroom effects are not dissociable. There is no cross-classification between teachers and classrooms (i.e., a teacher for the first grade will be solely responsible to this group of students). Moreover, all the classroom within the same school receives the same intervention (i.e., Elos 2.0 or treatment as usual).

This multilevel analysis will be dealt on Mplus version 8.4 under the maximum likelihood with robust standard errors (MLR). This estimator allows dealing with the non-independence of the observation (i.e., children nested classrooms); the standard error will be computed considering such multilevel structure by command in Mplus called (TYPE = Complex) using a sandwich estimator where the cluster variable will the classroom (i.e., teachers level) [43]. Adopted statistical significance was 0.05. Important to note that although within the school with have different classroom, all the classrooms within the same school are receiving either Elos 2.0 or treatment as usual to avoid contamination among the teachers. Therefore, our analysis will be following a two-level approach. In case of moderate or strong differences or unbalanced proportions between the control/intervention schools and/or children features on baseline measurements, the later will be inserted as covariates in the model for estimating the intervention effects. The only exception will be the baseline values of the outcome variables, which will be included in the within part as a predictor of the targeted outcome. This approach is also called the residualized change score [44].

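### City defines the randomisation but is not a fixed term in the primary model, and other covariates enter only on an undefined baseline imbalance, at odds with the unconditional list elsewhere

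*Protocol article*

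**What the plan says.** **Randomisation.** Trial design {8} has the study "performed in 30 schools in three cities (15 controls and 15 in the experimental group"). Explanation for the choice of comparators {6b} allocates schools "at a ratio of 1:1 control and experimental schools per municipality", and Concealment mechanism {16b} adds: "Randomization within each city will be performed when all schools are recruited for that city". The tool is Efron's biased coin (Sequence generation {16a}). The article does not use the word stratum, but city works as one.

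**Model.** Statistical methods for main outcomes {20a} makes covariate adjustment conditional: "In case of moderate or strong differences or unbalanced proportions between the control/intervention schools" and/or children's features at baseline, those features are added. One variable escapes the condition: "The only exception will be the baseline values of the outcome variables, which will be included in the within part as a predictor". City is therefore not a fixed term.

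**Covariates elsewhere.** Plans for assessment and collection of outcomes {18a} attaches no condition: "We will control for covariates, such as the gender and age of teachers and children, and the teachers’ stress levels and senses of self-efficacy". City is not on that list, which is left open. The abstract also says that the analysis controls for sociodemographic variables.

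**The concern.** There are three linked problems.

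1. When allocation is balanced within city, differences between cities largely cancel out of the treatment contrast. A model without city still counts that variation as noise, so its standard error is larger than the design warrants. The imbalance rule does not help: 1:1 allocation within city means that city will rarely look imbalanced, so the rule tends to leave out the one factor that the design itself makes relevant.

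2. In a randomised trial, baseline differences between arms arise by chance. A rule that adds covariates when such differences look large, without saying how large or for which variables, lets chance and later judgement settle the primary model.

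3. {18a} and {20a} read differently. One says that named covariates will be controlled for; the other says that covariates enter only if imbalanced.

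At stake are some precision and the ability to show that the primary estimate came from a model fixed in advance.

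**Working it through.** **Inputs from Sample size {14}.** Difference 0.25, SD 0.80, ICC 0.05, average m = 100 children per school, k = 15 schools (read as per arm), CV of cluster sizes 0.70, alpha 0.05 (taken as two-sided).

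**Step 1: reproduce the stated power.**
- Between-school variance B = 0.05 × 0.80² = 0.032. Within-school variance W = 0.95 × 0.80² = 0.608, so W/m = 0.00608.
- L = 0.032 / (0.032 + 0.00608) = 0.840. Relative efficiency for unequal clusters RE = 1 − CV² × L(1 − L) = 0.934.
- SE = √[2(B + W/m) / (k × RE)] = √[2 × 0.03808 / (15 × 0.934)] = 0.0737.
- Power = Φ(0.25/0.0737 − 1.96) = 92.4%, which matches the stated 92%.

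**Step 2: city omitted or included.** Let s be the share of between-school variance due to city. The article gives no value, so s is an assumption and includes zero. With balance within city, the estimate's true sampling SD is the SE with B replaced by B(1 − s) and RE recomputed. The model without city still reports 0.0737. Power with city omitted is 1 − Φ((1.96 × 0.0737 − 0.25)/SE with city). All rows assume standard errors that reflect clustering by school.

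| s (assumed) | SE, city omitted | SE, city included | CI wider without city | Power omitted | Power included |
|---|---|---|---|---|---|
| 0 | 0.0737 | 0.0737 | 0% | 92.4% | 92.4% |
| 0.10 | 0.0737 | 0.0707 | 4% | 93.2% | 94.2% |
| 0.25 | 0.0737 | 0.0660 | 12% | 94.5% | 96.6% |
| 0.50 | 0.0737 | 0.0571 | 29% | 96.8% | 99.2% |

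For example, 0.0737/0.0660 = 1.117; put the other way, the interval with city is about 10% narrower at s = 0.25.

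A simulation of 30 schools with t tests agrees. At s = 0.25, power without and with city is 92.4% and 95.5% for 10/10/10 schools per city, and 91.3% and 94.4% for 6/6/18. The number of schools per city is assumed, because the article does not give it.

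**Step 3: the imbalance rule.** The same simulation used three independent school-level covariates that together explain 30% of the remaining between-school variance (all assumed), with s = 0 and no treatment effect.
- One fixed cut-off of 0.5 SD: type I error 3.7% (10/10/10) and 4.1% (6/6/18), so no inflation.
- Smallest p value among no adjustment and cut-offs of 0.2, 0.5 and 0.8 SD: 6.8% and 7.1%.

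The harm therefore comes from leaving the threshold open, not from a fixed threshold as such.

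**The case against.** **The cost may be nil.** The baseline outcome is always in the model and will absorb lasting differences between cities in TOCA scores. What remains may be close to zero, and the calculation above takes no credit for that adjustment. This stands: the table shows what could be lost, not an estimate for this trial. The 92% power also stands without city.

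**A threshold and final covariate list can wait for the analysis plan.** This is fair as regards a missing cut-off. But {20a} does not stay silent. It states an imbalance-driven rule and names its only exception, so the type of rule is already fixed, and fixed badly.

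**{18a} may only list candidates.** It is a data-collection section with an open list, and {20a} can be read as the rule for admitting them. It is too strong to say that {18a} specifies a rival primary model. The unconditional wording still conflicts with the conditional rule.

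**Stronger readings the article does not support.**
- A reader might infer that the planned test is conservative because city is omitted. That needs school-level standard errors, whereas {20a} clusters on the classroom. In units of total variance, assume four classes of 25 per school, all the ICC at school level and s = 0.20. The planned variance per arm is then (0.05 + 0.95/25)/60 = 0.00147, against a true (0.04 + 0.95/100)/15 = 0.0033. The SE ratio is 0.667 and a nominal 5% test runs near 19%. Classroom clustering is a separate matter, but it rules out any claim that the test as written is conservative.
- A reader might infer that end-of-study teacher stress or self-efficacy would be adjusted for. {20a} limits added covariates to baseline measurements, and the participant timeline does not name either scale at follow-up.

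**Conclusion.** The point holds as a matter of precision and pre-specification, not bias. City governs the randomisation but is not a fixed model term, and the rule for other covariates depends on chance imbalance with no stated threshold or closed list. Given standard errors that reflect school-level clustering, leaving city out can only lose precision: none if cities do not differ after baseline adjustment, a confidence interval about 4% wider at an assumed 10% city share, and about 12% wider at 25%. The share is an assumption throughout, as is near-balance of arms within city. Type I error is at risk from the covariate rule only if the cut-off is chosen after seeing results; the roughly 7% in that case rests on the assumed covariates and cut-offs. {18a} and {20a} need one consistent statement. The change is worth making because it is almost free, not because the design fails without it.

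**What to change.** - In {20a}, define the primary model as arm, city (two indicators), baseline value of the outcome, and a short closed list of baseline covariates drawn from those the article already names, all entered whatever the observed balance.
- Delete the imbalance-triggered rule, or move it to a sensitivity analysis with a stated cut-off and candidate list.
- Align {18a} with {20a} so that both give the same list, and state that any teacher measures enter at baseline values only.

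The cost is wording and two degrees of freedom for city. In the simulation with no city differences at all, adding city changed power from 89.4% to 89.2% (10/10/10 schools) and from 90.0% to 89.9% (6/6/18). No data collection changes.

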### Interim analyses {21b}

Not applicable. This trial does not have a longer duration of recruitment or potentially serious outcomes. However, the Brazilian Ministry of Health can audit our protocol anytime.

### Methods for additional analyses (e.g., subgroup analyses) {20b}

For qualitative data, we will perform content analyses based on grounded theory using the NVivo 10 software programme. For qualitative variables, the summary measures with be the number and percentage. For numerical variables, the summary measures will be the mean, standard deviation, median, minimum and maximum. The integration of parallel databases will be performed via pairing of the secret codes using the Levenshtein algorithm. There is no analysis planned for any subgroup to identify interactions between the intervention and baseline participant characteristics, such as age or gender.

### Methods in the analysis to handle protocol non-adherence and any statistical methods to handle missing data {20c}

We will compose a letter-number code for each subject based on the school and personal information to maintain confidentiality and blinding in the data analyses. We will perform double data entry in the dataset and multiple imputation to handle missing data from the follow-up of participants which do not refuse to participate at the beginning or do not decline to perform the implementation. Missing data in the follow-up could occur if the child misses school on the data collection or if the child changes of school or city, which is likely to occur in any longitudinal drawing. Two different techniques will be used and contrasted: multiple imputation and the complier-average causal effect (CACE), which provide a form of sensitivity analysis of our intervention effects [45, 46]. CACE will be calculated by using data from the fidelity forms answered weekly by the teachers. Non-adherence will not consider the classroom where the teacher did not complete the program or have not delivery at least 50% sessions of Elos.

Multiple imputation operates under the assumption that the underlying missing mechanism is *missing at random* (MAR) and here multiple imputation will be carried out using Bayes estimation of an unrestricted variance-covariance model, where all of the main assessments of baseline sociodemographic and school features in the data set will be assumed as dependent variables. The variables with missing values will be included in the imputation step. The number of data sets to be imputed will depend on the fraction of missing information [42]. In case of missing data on child primary outcome (follow-up), they will be imputed. We do not expect child missing data at baseline outcome, but situation as loss of questionnaires, parents giving up of the children participations might happen requiring imputation of baseline primary outcome assessment. Multiple imputation is in accordance with intention-to-treat paradigm (ITT) broadly advocated by CONSORT [44]. We will perform an analysis using the ITT principle (all participants will be analysed as randomized, irrespective of whether they received the intervention in the intervention group) with observed data only, and a further ITT analysis using observed and imputed data. The primary analysis will be with the ITT using observed data only.

To deal with missing data from teachers who decline to participate after the training and partial implementation (i.e., absence of answers in questionnaires) CACE will be contrasted to the traditional intention-to-treat approach [47]. CACE involves a mixture modelling [48], which allows us to robustly estimate the effect of the intervention among those who were compliers in the intervention group versus those who were potential compliers among those in treatment as usual group. The status of adherent (or not) is not directly observable among those in control group because the participants were not exposed to the intervention. Therefore, one should use latent variable modelling to uncover the status of the participants in such a group. Major details about CACE modelling might be found in [49, 50]. As a sensitivity analysis, a CACE analysis will be performed using the adherence data for each teacher (i.e., each teacher and pupil in the intervention group will be considered as a “complier” or “non-complier”).

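### The imputed ITT analysis leaves out intervention classes that decline to implement, and CACE cannot stand in for their missing follow-up

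*Protocol article*

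**What the plan says.** All of this is in the protocol article, mainly section {20c} on non-adherence and missing data.

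- **Primary analysis.** "The primary analysis will be with the ITT using observed data only".
- **Supporting analysis.** The plan adds "a further ITT analysis using observed and imputed data". ITT is defined as "all participants will be analysed as randomized, irrespective of whether they received the intervention in the intervention group".
- **Who is imputed.** Imputation of missing follow-up is for "participants which do not refuse to participate at the beginning or do not decline to perform the implementation".
- **Decliners.** {20c} expects some teachers to decline after training and partial implementation and to leave questionnaires unanswered. It deals with those missing data by contrasting CACE with ITT. Earlier, it presents imputation and CACE as two techniques to be compared.
- **CACE.** The model compares "compliers in the intervention group versus those who were potential compliers among those in treatment as usual group", and "each teacher and pupil in the intervention group will be considered as a “complier” or “non-complier".
- **Under-delivery.** "Non-adherence will not consider the classroom where the teacher did not complete the program or have not delivery at least 50% sessions of Elos".

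Elsewhere, {11b} (discontinuing or modifying interventions) says that teachers and students who drop out after baseline still supply follow-up. Outcomes {12} and the participant timeline {13} make the teacher the TOCA-C rater, with an interviewer mediating. Trial design {8} gives control schools no behavioural programme.

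**The concern.** Who is imputed depends on something that happens after randomisation and in one arm only. A control teacher cannot decline to implement a programme that was never offered. A rule of that kind conflicts with the ITT definition in the same section, which disregards whether the intervention was received.

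The outcome source makes this more than a matter of labels. If a declining teacher stops answering questionnaires, follow-up for the whole class is lost. Those children are then absent from the observed-data primary analysis, and the imputation rule keeps them out of the analysis meant to bring them back. The check would share the gap that it is supposed to test.

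Sending these data to CACE does not close the gap. CACE estimates the effect in classes that deliver, or would have delivered, the programme. The ITT effect averages over all classes, including those that did not. A CACE result therefore cannot show what the ITT result would have been with complete follow-up.

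**Working it through.** **The plan's own figure.** Sample size {14} gives a difference of 0.25, SD 0.80, ICC 0.05, mean cluster size 100, coefficient of variation (CV) of cluster size 0.70 and 1,500 children per arm. I read the 15 clusters as per arm and alpha as two-sided.

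- L = 100×0.05 / (100×0.05 + 0.95) = 0.840
- Design effect = (1 + 99×0.05) / (1 − 0.70²×0.840×0.160) = 5.95 / 0.934 = 6.37
- SE = 0.80×√(2×6.37/1500) = 0.0737
- Power = Φ(0.25/0.0737 − 1.96) = 92.4%

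The stated 92% reproduces. It does not bear on this point; only 0.25 and 0.80 are carried forward.

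**The rules side by side.**

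| Question | ITT definition, {20c} | Imputation rule, {20c} | {11b} |
|---|---|---|---|
| Does declining to implement matter? | No | Yes, no imputation | No, follow-up still supplied |
| Which arm can be affected? | Neither | Intervention only | Neither |

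The first two columns cannot both govern one analysis. The third disagrees with the later part of {20c}, which expects decliners' questionnaires to be missing.

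**Size.** The documents give no decline rate, so these inputs are assumed: a share q of intervention classes declines, gets no benefit and has no follow-up; class sizes are equal; the effect where the programme is delivered is 0.25; declining classes would in any case be g SDs worse than the others. The control arm keeps its counterparts of the declining classes.

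- ITT effect = (1 − q)×0.25
- Estimate without the declining classes = 0.25 + q×g×0.80
- Excess over ITT = q×0.25 + q×g×0.80

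| q | ITT effect | Excess, g = 0 | Excess, g = 0.25 | Spurious effect if Elos does nothing, g = 0.25 |
|---|---|---|---|---|
| 10% | 0.225 | 0.025 | 0.045 | 0.02 |
| 20% | 0.200 | 0.050 | 0.090 | 0.04 |
| 30% | 0.175 | 0.075 | 0.135 | 0.06 |

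With g = 0 the excess is 10–30% of the 0.25 target. The direction also depends on g: the excess is zero at g = −0.25/0.80 = −0.31, and changes sign if declining classes would have been better than the rest by more than that.

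**The case against.** The strongest defence is that the rule limits who is imputed and deletes nothing. Observed data from declining classes stay in, and {11b} expects drop-outs to supply follow-up. If they do, the rule has almost nothing to act on. This stands, and it is why the size is conditional. It does not remove the conflict, because {20c} itself plans for decliners who leave questionnaires blank. The wording is also loose: the word joining its two conditions could be read as requiring only one of them. But the section then gives decliners' missing data to CACE, so reading both as required fits better.

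A reader might go further in three ways that the article does not support.

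- **That CACE drops under-delivering classes and becomes a per-protocol comparison.** The 50%-of-sessions sentence can be read so, but it is garbled and may equally be meant to define the non-adherent group. The later text classes every intervention teacher and pupil, within a mixture model that treats compliance in controls as latent. That keeps non-compliers in. The fault is an unclear sentence.
- **That the imputation model omits arm and school.** The plan says "multiple imputation will be carried out using Bayes estimation of an unrestricted variance-covariance model" and lists baseline sociodemographic and school features. Arm and cluster level are not mentioned, but neither is said to be excluded, and such a model can have one level or two. A condensed article may leave this to the analysis plan. If arm were left out with a fraction f of follow-up missing, 0.25 would shrink to about 0.25×(1 − f), or 0.20 at an assumed 20%; nothing shows that it is.
- **That both supporting analyses are biased.** The imputed analysis can be, under the conditions above. The imputation rule does not by itself reach the CACE model.

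**Conclusion.** The point holds in a limited form. Restricting imputation to those who do not decline contradicts the section's own ITT definition, acts on the intervention arm only, and can bias the imputed check. CACE answers a different question and cannot replace imputation for the ITT effect.

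The excess of 0.025–0.075 rests on assumed decline rates of 10–30%, no benefit in declining classes and complete loss of their follow-up. It rises to 0.045–0.135 if those classes are also 0.25 SD worse, and is near zero if {11b} is honoured in practice. The definition of the primary observed-data ITT analysis does not change. This should be corrected before analysis, as a fault in a supporting analysis and not in the main one.

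**What to change.** 1. Impute follow-up TOCA-C for every randomised, consented child, whether or not the class implemented the programme.
2. Stop describing CACE as a way to handle missing data. Keep it as a sensitivity analysis for non-adherence.
3. Reword the 50%-of-sessions sentence so that classes which did not complete, or delivered under half, are coded as non-compliers and kept in the CACE model, as the later text implies.
4. Reconcile {11b} and {20c} on whether decliners supply follow-up. Imputation under missing at random would tend to fill a wholly unobserved declining class from classes that did deliver. It can restore differences that baseline explains, but not an absent benefit, so follow-up actually obtained from decliners matters most.
5. It is advisable to state that arm and school clustering enter the imputation model, though their absence from this article is not shown to be an error.

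The cost is a few sentences and modest programming. No data are needed beyond the follow-up that {11b} already expects.
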